#### Primary outcome

The primary outcome will be cognitive functioning, which will be assessed by the MCCB for measuring cognition in schizophrenia. The MCCB embraces the main cognitive domains affected in schizophrenia [25], namely (1) speed of processing measured by *Brief Assessment of Cognition in Schizophrenia* (BACS): *Symbol Coding* (a timed paper-and-pencil test in which the respondent uses a key to write digits that correspond to nonsense symbols), *Category Fluency: Animal Naming* (a test in which the respondent names as many animals as she/he can in 1 min), and the *Trail Making Test*: Part A (a timed paper-and-pencil test in which the respondent draws a line to connect consecutively numbered circles placed irregularly on a sheet of paper); (2) attention/vigilance measured by the *Continuous Performance Test-Identical Pairs* (CPT-IP), a computer-administered measure of sustained attention in which the respondent presses a response button to consecutive matching numbers; (3) working memory measured by the *Wechsler Memory Scale*®*-3rd Edition* (WMS®-III): *Spatial Span* (using a board on which 10 cubes are irregularly spaced, the respondent taps cubes in the same (or reverse) sequence as the test administrator) and *Letter*–*Number Span* (orally administered test in which the respondent mentally reorders strings of numbers and letters and repeats them to the administrator); (4) verbal learning measured by the *Hopkins Verbal Learning Test-Revised*™ (HVLT-R™), which is an orally administered test in which a list of 12 words from three taxonomic categories is presented and the respondent is asked to recall as many as possible after each of three learning trials; (5) isual learning measured by the *Brief Visuospatial Memory Test-Revised* (BVMT-R™), which is a test that involves reproducing six geometric figures from memory; (6) reasoning and problem solving measured by the *Neuropsychological Assessment Battery*® (NAB®), which consists of mazes; the task is composed of seven timed paper-and-pencil mazes of increasing difficulty that measure foresight and planning; (7) *Mayer-Salovey-Caruso Emotional Intelligence Test* (MSCEIT™), a paper-and-pencil multiple-choice test that assesses how people manage their emotions.

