## Methods/design

### Trial design

The design of the present study protocol is a double-blind, placebo-controlled randomized clinical trial.

After being randomly allocated, the experimental group will receive 20 min of active 2-mA tDCS once a day for 10 consecutive weekdays. The control group will receive a sham stimulation (placebo); the chosen parameters are that, after 40 s of real stimulation (2 mA), only a small current pulse occurs every 550 ms (110 mA over 15 ms) through the remainder of the 20-min period.

Neuropsychological and psychiatric assessments will be performed at the time of consent (baseline) and at 1 and 3 months following the end of the intervention (maintenance effect). The primary outcome will be cognitive function; the secondary outcomes will be the positive and negative symptoms. Outcome assessments will be performed by trial research staff. Primary and secondary outcome assessors (neuropsychologists and psychiatrists) and patients will be blinded to randomized allocation after assignment to the interventions.

The present study protocol was written in compliance with the Standard Protocol Items: Recommendations for Interventional Trials (SPIRIT) 2013 [9]. A completed SPIRIT checklist is available as a supplement (Additional file 1), and the schedule of this study is presented in Fig. 1. The study flowchart is shown in Fig. 2.

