### Statistical analyses

The data will be analyzed with the Statistical Package for Social Sciences (SPSS 18.0, Chicago, IL, USA). Statistical significance will be set at *p* < 0.05 (two-tailed) for all analyses.

Student’s *t* test will be used in comparisons involving continuous clinical and sociodemographic variables with normal distribution and the Mann-Whitney test for comparisons involving clinical and sociodemographic data with non-normal distribution. Comparisons involving categorical variables will be performed using the chi-square test.

Analysis of Covariance (ANCOVA) with repeated measures, with intervention group used as intersubject factor, neuropsychological scores from MCCB tests as intrasubject factors, and years of education as a covariate, will be performed to evaluate the efficacy of intervention in the treatment of cognitive deficits (primary outcome). The same analysis, using PANSS negative and positive subscale scores as intrasubject factors and duration of illness as a covariate, will be performed to evaluate the efficacy of intervention in the treatment of negative and positive symptoms (primary outcome).

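### The primary outcome is a whole cognitive battery at two follow-up visits with no score, visit or model term named as deciding, so the stated 5% error and 80% power attach to no identifiable endpoint

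*Protocol article*

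**What the plan says.** All references are to the protocol article.

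- **Primary outcome:** "The primary outcome will be cognitive functioning, which will be assessed by the MCCB for measuring cognition in schizophrenia". The section then numbers seven domains, measured by ten tests: Symbol Coding, Animal Naming, Trail Making A, CPT-IP, Spatial Span, Letter-Number Span, HVLT-R, BVMT-R, NAB mazes and MSCEIT. No composite, lead domain or lead test is named.
- **Trial design and Outcome measures:** assessments are at baseline and "at 1 and 3 months following the end of the intervention". Neither follow-up visit is singled out.
- **Statistical analyses, threshold:** "Statistical significance will be set at *p* < 0.05 (two-tailed) for all analyses". No adjustment or testing order is given.
- **Statistical analyses, model:** a repeated-measures ANCOVA with intervention group between subjects and "neuropsychological scores from MCCB tests as intrasubject factors, and years of education as a covariate". Time is not named as a factor, and the group effect that decides efficacy is not stated.
- **Statistical analyses, PANSS:** the same analysis of the PANSS subscales is labelled as addressing the primary outcome. Trial design and Secondary outcomes both call those symptoms secondary.
- **Power and sample size calculation:** effect size 0.8, SD 1.0 for one outcome, Zα = 1.95996, Zβ = 0.84162, with 10% non-adherence and 10% drop-out, giving 70 patients (35 per group).

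**The concern.** The endpoint, the threshold and the sample size are each stated, but they do not fit together. A single test at two-sided 0.05 with 80% power needs one variable, one time point and one contrast. The document gives a battery, two visits and a model whose deciding term is open. The result that counts as primary could then be settled after the data are seen, and a reader of the final report could not tell whether it was. The PANSS analyses labelled primary widen the undefined family further.

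**Working it through.** **1. Reproduce the stated sample size.** Inputs from Power and sample size calculation:

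n per arm = 2(1.95996 + 0.84162)² / 0.8² = 2 × 7.849 / 0.64 = 24.5, so 25 (26 with the noncentral t).

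Take non-adherence as dilution of the effect, 1/0.9², and drop-out as 1/0.9: 25 / 0.729 = 34.3, so 35 per arm and 70 in total. The stated figure is reproduced (the t version gives 36 per arm, 72 in total). It is a calculation for one comparison at the full two-sided 0.05.

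**2. One model over the whole battery.** This was simulated under the null with 35 per arm, three visits, between-visit correlation 0.7, correlation between tests 0.3 to 0.7, and 4,000 runs. The education covariate was left out.

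| What may count as success | Chance of a false positive |
|---|---|
| One named term (group-by-time) | 4.3% to 5.5% |
| Either group or group-by-time | 8.7% to 10.7% |
| Any of four group terms, taken as independent | 1 − 0.95⁴ = 18.5% |

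**3. Domains or tests judged separately, any one counting.** For m independent tests the chance is 1 − 0.95^m:

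- m = 7 (domains, one visit): 30.2%
- m = 10 (tests, one visit): 40.1%
- m = 14 (domains, two visits): 51.2%
- m = 20 (tests, two visits): 64.2%

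For correlated two-sided z-tests (200,000 runs; equal correlation between tests; between-visit correlation 0.7 where two visits are counted):

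| Family | Correlation 0.3 | Correlation 0.5 | Correlation 0.7 |
|---|---|---|---|
| 7 domains, one visit | 27.0% | 23.0% | 17.8% |
| 10 tests, one visit | 35.1% | 28.7% | 21.3% |
| 7 domains, two visits | 41.7% | 35.5% | 27.9% |
| 10 tests, two visits | 51.9% | 43.4% | 33.0% |

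If each domain or test has its own repeated-measures model judged on group-by-time, the visits are not separate tests. The chance is then 28% to 18% for seven and 35% to 23% for ten, over the same correlations.

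**4. What the remedies do.**

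- One composite at one named visit and one contrast gives 5%, and N stays at 70.
- One composite tested at both visits gives 7.8% to 9.1% (between-visit correlation 0.8 to 0.5), so the visit has to be named as well.
- Keeping all domains or tests as primary with Bonferroni cuts power for each one, at the uninflated 26 per arm, from 81% to 54% (seven, α = 0.05/7) or 49% (ten, α = 0.05/10).

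**The case against.** A reader might infer that the trial's false-positive rate is 25-50% rather than 5%. The document does not support that as a flat statement, for three reasons.

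- It sets a threshold and a model but no rule that any one significant test is a success.
- The plural wording "neuropsychological scores from MCCB tests as intrasubject factors" can be read literally as one model over the battery, and step 2 then applies.
- Nothing says the two visits are tested separately, since a repeated-measures model can combine them. The correlations between tests and between visits are not given either.

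A reader might also infer that the trial is underpowered. That does not follow. The calculation fits a single cognitive summary and is unchanged once one is named. The defect is an unnamed endpoint, not a demonstrated shortfall.

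Finally, this article condenses a fuller protocol, and composite scoring or multiplicity rules may stand there or in an analysis plan. That would excuse silence. It does not excuse what the article does fix: a battery as the primary outcome, unadjusted 0.05 throughout, and a sample size for one outcome. The one-model reading does not rescue the text either. It reaches 5% only with one named group term, and none is named. Applying the same analysis to the two PANSS subscales, and a hypothesis worded in terms of cognitive processes in the plural, leave separate testing open.

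**Conclusion.** The point holds as an undefined primary endpoint, and it should be corrected before unblinding. No single score, visit or model term is identified, so the stated 5% error and 80% power have nothing definite to refer to.

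The inflation is conditional on the reading. It is about 5% (none) for one battery model with one named term, and about 10% if either of two terms may count. It is roughly 20-50% if domains or tests are judged separately and any one suffices. That last range rests on assumed correlations of 0.3 to 0.7. Its upper part also needs the two visits to be counted as separate tests, with an assumed between-visit correlation of 0.7. Confidence is high in the defect and lower in any single figure for its size.

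**What to change.** 1. In Primary outcome, name one variable, the MCCB overall composite (the mean of the standardised domain scores, all scored in the same direction), at one visit (1 or 3 months).
2. In Statistical analyses, replace the primary model with one that tests a single stated group contrast on that composite at that visit, at two-sided 0.05. A model with individual test scores as within-subject factors does not do this.
3. Make the other visit and the seven domain scores secondary, with Holm adjustment across the domains.
4. Relabel the PANSS analyses in Statistical analyses as secondary, to agree with Trial design and Secondary outcomes.
5. In Power and sample size calculation, say that the effect size of 0.8 and SD of 1.0 refer to the named endpoint. N = 70 is unchanged.

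If the sponsor prefers several co-primary domains or tests, the multiplicity procedure must be stated and the power recomputed.

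The cost is wording in the protocol and analysis plan before unblinding. The small downside is that an effect in a single domain can no longer be claimed as primary success.

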#### Secondary outcomes

The secondary outcomes will be positive and negative symptoms. Symptom severity will be assessed by means of the Positive and Negative Syndrome Scale (PANSS) [20]. Trained psychiatrists will conduct all interviews.

### Power and sample size calculation

The sample size calculation was performed by using the *T* statistic and non-centrality parameter. The expected effect size of 0.8 was conservatively estimated on the basis of the results of more recently published studies [10]. The basis of the sample size estimation is an expected cognitive improvement of about 35% in the tDCS intervention group. The sample size was calculated assuming an aimed power of 80% and a standard deviation of the outcome in the population of 1.0 (standard normal deviate for α = Zα = 1.95996; standard normal deviate for β = Zβ = 0.84162). After consideration of a non-adherence rate of 10% and a drop-out rate of 10% in both arms, the case number results in 70 patients (35 patients per group).

### Group allocation

Subjects will be allocated to the experimental and control groups in a 1:1 ratio, by using the sequence generated by http://www.randomisation.com. The allocation sequence will be generated by a technician who will not be involved in the neuropsychological or psychiatric assessments. The staff in charge of delivering the tDCS/sham intervention will be informed of the treatment allocation.

### Blinding

Application of the assigned treatment will be carried out after the neuropsychological and psychiatric assessments. A double-blinding arrangement will be conducted in this clinical trial. Primary and secondary outcomes raters (neuropsychologists and psychiatrists) and patients will be blinded to randomized allocation after assignment to interventions. The tDCS/sham intervention will be delivered by an independent research staff.

### Ethical approval

This study protocol was approved by the Ethics Committee of the Federal University of Sao Paulo, in Sao Paulo, Brazil, and written informed consent will be obtained from all participants in the trial (see Additional file 2).

The results will be presented at scientific meetings and published in periodicals.

### Statistical analyses

The data will be analyzed with the Statistical Package for Social Sciences (SPSS 18.0, Chicago, IL, USA). Statistical significance will be set at *p* < 0.05 (two-tailed) for all analyses.

Student’s *t* test will be used in comparisons involving continuous clinical and sociodemographic variables with normal distribution and the Mann-Whitney test for comparisons involving clinical and sociodemographic data with non-normal distribution. Comparisons involving categorical variables will be performed using the chi-square test.

Analysis of Covariance (ANCOVA) with repeated measures, with intervention group used as intersubject factor, neuropsychological scores from MCCB tests as intrasubject factors, and years of education as a covariate, will be performed to evaluate the efficacy of intervention in the treatment of cognitive deficits (primary outcome). The same analysis, using PANSS negative and positive subscale scores as intrasubject factors and duration of illness as a covariate, will be performed to evaluate the efficacy of intervention in the treatment of negative and positive symptoms (primary outcome).

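### Unless missing scores are imputed first, the primary repeated-measures ANCOVA uses only patients with complete data; at the planned 10% drop-out it leaves out about 7 of 70 randomised patients

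*Protocol article*

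**What the plan says.** Under Statistical analyses, the primary outcome is to be tested by "Analysis of Covariance (ANCOVA) with repeated measures, with intervention group used as intersubject factor", with "neuropsychological scores from MCCB tests as intrasubject factors, and years of education as a covariate". The package is SPSS 18.0. The same form of analysis is planned for the PANSS positive and negative subscales, with duration of illness as the covariate.

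Under Trial design, assessments take place "at the time of consent (baseline) and at 1 and 3 months following the end of the intervention (maintenance effect".

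Under Power and sample size calculation, the effect size is 0.8, "assuming an aimed power of 80% and a standard deviation of the outcome in the population of 1.0". The allowance for losses is given as "After consideration of a non-adherence rate of 10% and a drop-out rate of 10% in both arms", which brings the stated total to 70, or 35 per arm. Drop-out is used there to raise the sample size. The article does not say how patients with missing scores enter the primary analysis. Under Intervention, participants may ask to stop at any time; under Participants, regular phone contact is planned to help retention.

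**The concern.** Intersubject and intrasubject factors are the terms of the classical repeated-measures general linear model. That model needs a complete row for each patient. If one repeated score is missing, the whole patient is removed, including the scores that were observed. Someone assessed at 1 month and lost before 3 months would contribute nothing.

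The article itself expects drop-out, so patients would be lost if the named method is followed as it stands. Raising the sample size protects power but does nothing about who is left. The primary comparison would be between completers rather than between the groups as randomised. It would be biased if the reasons for leaving were related to response or tolerability and differed between arms. Equal drop-out rates in the two arms do not exclude this, because equal numbers can leave for different reasons.

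**Working it through.** **Inputs from the article:** effect size 0.8, SD 1.0, power 80%, Zα = 1.95996, Zβ = 0.84162, non-adherence 10%, drop-out 10%, total 70 (Power and sample size calculation); two follow-up visits (Trial design); repeated-measures ANCOVA (Statistical analyses).

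**1. The plan's own figure.** Per arm, n = 2 × ((1.95996 + 0.84162)/0.8)² = 24.53, rounded up to 25. The article does not print its inflation formula. If non-adherence dilutes the effect and drop-out removes patients, the divisor is 0.9² × 0.9 = 0.729, and 25/0.729 = 34.3, rounded up to 35 per arm, or 70 in total. This reproduces the stated figure. A t-based start of 26 gives 26/0.729 = 35.7, rounded up to 36 per arm, or 72. Treating both rates as simple loss does not reach 70: 26/0.80 = 32.5, rounded up to 33 per arm, or 66. The reconstruction that fits therefore keeps non-adherent patients in the analysis.

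**2. Patients lost.** 10% of 70 = 7, leaving about 63 (31.5 per arm).

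**3. Power after that loss** (two-sample t test, two-sided 5%):

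| Patients per arm | Effect (SD) | Power |
|---|---|---|
| 31.5 | 0.8 | 87.8% |
| 31.5 | 0.72 (= 0.9 × 0.8, diluted by 10% non-adherence) | 80.3% |

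The planned 80% is kept. Relative to analysing all 70, the standard error grows by √(1/0.9) = 1.054, about 5%, and the sample size already pays for this.

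**4. Possible bias.** If a fraction p of an arm is deleted and those patients differ from that arm's completers by k SD, the arm mean moves by p × k. The values of k are assumptions; the article gives none.

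| Assumption, p = 0.10 | Shift in group difference | Share of 0.8 |
|---|---|---|
| One arm, k = 0.5 | 0.05 SD | 6.25% |
| One arm, k = 1.0 | 0.10 SD | 12.5% |
| Both arms, opposite directions, k = 0.5 | 0.10 SD | 12.5% |
| Both arms, opposite directions, k = 1.0 | 0.20 SD | 25% |

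**5. Extreme illustration.** Suppose the 10% lost in the active arm are exactly its lowest scorers at 1 month, all of whom attended that visit, and loss in the sham arm is random. Removing the lowest tenth of a normal distribution moves its mean by 0.1755/0.9 = 0.195 SD. With an assumed correlation of 0.7 between visits, the 3-month shift is 0.7 × 0.195 = 0.137 SD. A simulation agrees: with no true difference, completers differ by 0.19 SD at 1 month and 0.13 SD at 3 months; with a true difference of 0.8 they differ by 0.99 and 0.93.

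**6. What a mixed model recovers.** In step 5 every drop-out has a 1-month score, so keeping those scores removes the 1-month shift, and the 3-month shift is corrected under missing at random. If instead all drop-outs were lost before 1 month, a model on follow-up scores would also have about 63 patients and gain nothing. The article does not say when drop-out is expected, so the gain lies between these two ends.

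**The case against.** **Analysis sets and missing data are often left to a fuller document.** This is a published article, and imputation before the ANCOVA would be compatible with its text. That stands, and it is why the point is conditional on no imputation. It does not remove the point, which concerns a method the article names rather than a detail it omits.

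**The pattern of deletion is inferred.** The article names MCCB scores, not visit, as the intrasubject factors. That stands too. It does not help the plan: Primary outcome lists ten tests, and if these were entered as levels, one missing test would also remove the patient.

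**Stronger readings that the documents do not support:**
- *Up to 14 of 70 patients would be lost.* This adds non-adherence to drop-out. The model deletes patients with missing scores, not patients who missed sessions; the article lists the two rates separately and states no per-protocol exclusion.
- *The trial would be underpowered.* The sample size already covers the expected loss (step 3).
- *Drop-out will be related to arm or response.* Nothing in the article shows this. It assumes the same rate in both arms, describes the technique as well tolerated, and plans contact to help retention. Related drop-out is a risk, not a known fact.
- *A shift of 0.2 SD is to be expected.* It needs either the selection constructed in step 5 or a full 1.0 SD difference in opposite directions in both arms.
- *A mixed model restores the full randomised comparison.* It does not for patients with no follow-up score.

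**Conclusion.** The point holds in a limited form. As written, and without prior imputation, the primary analysis would use about 63 of 70 randomised patients at the planned drop-out rate and would discard any 1-month scores from the other 7 or so. Power is not the issue.

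The issue is avoidable selection. Its size is unknown: 0.05 to 0.10 SD if drop-outs in one arm differ from its completers by 0.5 to 1.0 SD, and about 0.2 SD at the extreme, against a planned effect of 0.8 SD. These figures rest on assumed differences and on drop-out of 10%; the bias is zero if drop-out is unrelated to outcome. This does not invalidate the trial, but the method should be changed because a better one is available at little cost.

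**What to change.** Replace the repeated-measures ANCOVA with a linear mixed model for repeated measures (SPSS MIXED):

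- outcome: the MCCB scores at 1 and 3 months;
- fixed effects: group, visit, group-by-visit, baseline score, and years of education as already specified;
- unstructured covariance between visits, fitted by REML;
- population: all randomised patients with at least one follow-up score, as allocated and regardless of adherence.

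Add a simple sensitivity analysis for patients with no follow-up score. For example, impute their scores at 0, 0.5 and 1.0 SD below the value predicted from their arm and baseline, in one arm and then the other, and report whether the conclusion changes. Apply the same change to the PANSS analyses, keeping duration of illness as the covariate.

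The cost is a revised paragraph and a different procedure in the same software, with no extra patients or visits. The article describes the trial as ongoing, so the change should be fixed before the data are unblinded. The downside is reliance on missing at random, which is weaker than what a completers-only analysis generally needs but cannot be verified from the data.

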### Objectives

The aim of the present study protocol is to evaluate the efficacy of tDCS in the treatment of cognitive symptomatology in the early stages of psychosis. We hypothesized that the patients randomly allocated to the experimental group will demonstrate a significant better performance on cognitive processes in comparison to those in the matched control group.

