### Outcome measures

At all assessment interviews, including neuropsychological and psychiatric, at the time of consent (baseline), and at 1 and 3 months following the end of the intervention (maintenance effect), IQ estimate and functioning will be tested in addition to the collection of standard demographic information. For this purpose, the Wechsler Adult Intelligence Scale Third Edition (WAIS-III) and the Personal and Social Performance Scale (PSP) will be used.

The WAIS-III is a standardized instrument for measuring the intellectual functioning and overall capacity of an individual [30, 31]. In order to measure the estimated IQ of the subjects under study, two WAIS-III subtests were selected, one to measure verbal and crystallized intelligence (Vocabulary) and another to measure non-verbal and fluid intelligence (Matrix Reasoning).

The Vocabulary subtest of the WAIS-III is a measure of verbal knowledge and crystallized intelligence. The version that will be used consists of 33 items. The task is to define a certain term, for example, “what is a BED?”. The examinee must include in his answer essential characteristics that define the specified term. Simple correct answers, usually involving a concrete aspect of the term, are scored as score 1, and correct complex answers receive score 2. Incorrect answers are scored as 0 [31].

The Matrix Reasoning subtest of the WAIS-III is a measure of abstract reasoning and execution and fluid intelligence. The subtest has 26 items, plus the three that serve as examples. It consists of four types of items: continuous and discrete patterns, classification, analog reasoning, and serial reasoning. The task requested of the examinee is to complete a series of incomplete patterns, pointing out or saying the correct answer number among the five alternatives presented [31].

The PSP is a validated clinician-administered scale that measures personal and social functioning in the domains of (1) socially useful activities, including work and study; (2) personal and social relationships; (3) self-care; and (4) disturbing and aggressive behaviors [22].

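### The repeated-measures ANCOVA names test scores and PANSS subscales, not visit, as its within-subject factors, so as written its terms do not isolate the post-treatment group difference for each outcome

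*Protocol article*

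**What the plan says.** All references are to the protocol article.

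- **Statistical analyses, primary outcome.** A repeated-measures ANCOVA is planned "with intervention group used as intersubject factor, neuropsychological scores from MCCB tests as intrasubject factors, and years of education as a covariate". Its stated purpose is to judge efficacy on cognitive deficits.
- **Statistical analyses, symptoms.** The same analysis is to be run "using PANSS negative and positive subscale scores as intrasubject factors and duration of illness as a covariate".
- **Trial design.** Neuropsychological and psychiatric assessments "will be performed at the time of consent (baseline) and at 1 and 3 months following the end of the intervention".
- **Blinding.** "Application of the assigned treatment will be carried out after the neuropsychological and psychiatric assessments", so baseline scores carry no treatment effect.
- **Objectives.** The hypothesis is a between-group one: patients given active stimulation "will demonstrate a significant better performance on cognitive processes in comparison to those in the matched control group".

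Neither model sentence names visit or time, a group-by-visit term, the baseline score as a covariate, or the term on which efficacy is judged.

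**The concern.** In a repeated-measures model the within-subject factor is the dimension along which the same quantity is measured again. Here that is visit. A test score is the dependent variable. The article instead gives the scores the role of the factor, and it does so twice, the second time by naming two different PANSS subscales together.

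This is more than detail left to an analysis plan. The article states what the within-subject factor is, and what it states does not fit the design. It is also the only efficacy analysis given for the primary outcome. Taken literally, none of its standard terms is the post-stimulation group difference on one outcome. The choice among main effect, interaction and single tests could then be made after the results are seen.

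**Working it through.** **1. The plan's own figure.** From Power and sample size calculation: effect 0.8, SD 1.0, Zα = 1.95996, Zβ = 0.84162.

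n per arm = 2 × ((1.95996 + 0.84162)/0.8)² = 24.5, rounded up to 25.

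The article does not say how it inflates for 10% non-adherence and 10% drop-out. Dividing by 0.9² × 0.9 = 0.729 gives 25/0.729 = 34.3, so 35 per arm and 70 in all. The stated total is therefore reproduced and is not in dispute. It belongs to a two-group comparison of a single outcome.

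**2. Group-by-score interaction, scores as levels.** Let δ_k be the standardised group difference on test k. The interaction tests δ_1 = δ_2 = … = δ_K. If every δ_k is 0.8, all contrasts δ_j − δ_k are 0. A simulation (3,000 runs; 7 scores; inter-score correlation 0.4; 28 per arm; equal benefit on all scores at both follow-ups) gave rejection rates of 5.4%, 5.7% and 4.8% at visit correlations 0.5, 0.7 and 0.8. That is the significance level and no more.

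**3. Group main effect, scores as levels.** This is the mean of the δ_k. If all three visits enter, it is also averaged over visits: (0 + 0.8 + 0.8)/3 = 0.8 × 2/3 = 0.53.

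If scores were entered raw, the average would also mix units. The battery includes a timed trail test beside a count of animals named, and these can move in opposite directions if the first is scored as time taken. The article does not say whether scores are raw or standardised.

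**4. PANSS model.** With the two subscales as levels, the group main effect is (δ_neg + δ_pos)/2 and the interaction is δ_neg − δ_pos. Neither is δ_neg or δ_pos, the two secondary outcomes.

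**5. Power.** Assumptions not in the article: 28 analysed per arm (35 × 0.8), 0.8 SD at both follow-ups, 0 at baseline, visit correlation r. The benchmark, a single-visit t test at d = 0.8, has 84% power.

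(a) One score or composite, group main effect over three visits. SD of the mean = √((1 + 2r)/3), so d = 0.533/SD.

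| r | d | power |
|---|---|---|
| 0.6 | 0.623 | 63% |
| 0.7 | 0.596 | 59% |
| 0.8 | 0.573 | 56% |

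(b) The same term averaged over 7 standardised scores, each with a 0.8 SD benefit, inter-score correlation c. The SD is multiplied by √((1 + 6c)/7).

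| c | multiplier | d (r = 0.8 to 0.6) | power |
|---|---|---|---|
| 0.4 | 0.697 | 0.82–0.89 | 86–91% |
| 0.6 | 0.811 | 0.71–0.77 | 74–81% |
| 0.8 | 0.910 | 0.63–0.68 | 64–71% |

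The reduction from 0.8 to 0.53 is the same in (a) and (b). The power is not.

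**6. Baseline imbalance.** With no treatment effect but a stable 0.4 SD gap present from baseline (simulated at r = 0.7), the group main effect was significant in 38% of runs and group-by-visit in 5%. This is conditional on such a gap having arisen. It shows that the main effect cannot tell a chance baseline gap from a treatment effect.

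**The case against.** The best defence is that the wording is loose rather than the model wrong. The phrase about repeated measures, together with three fixed assessments, may mean that each score is followed over visits. The plural factors may then just be the variables entered in the SPSS procedure, one analysis per score and per subscale. That reading is possible. The text does not say it, however, and under it the factor is still misnamed and the efficacy term is still unstated.

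Two stronger inferences are tempting, and the article supports neither.

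- *That power falls to 56–63% instead of 80%.* Those figures arise only when the overall group main effect over three visits is read for a single score or composite (step 5a). A model with visit correctly named gives the same figures if that term is read. Averaging over several tests can give more than 80% (step 5b). The article gives none of the correlations.
- *That the model cannot estimate a treatment effect at all.* Run on one post-treatment visit, its group main effect would be a valid contrast averaged over tests, though not adjusted for baseline. The article states no such restriction, but the absolute claim is still too strong.

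It is also fair that score scaling and the choice of a composite may properly sit in an analysis plan. Leaving them out is not the fault here.

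**Conclusion.** The point stands as a wrongly stated model in the only efficacy analysis the article gives. Three consequences follow from the text as written:

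- the interaction is blind to a benefit that is equal, in standardised terms, across tests;
- the main effect averages over tests and, if all visits enter, targets 0.53 SD where the follow-up difference is 0.8 SD;
- positive and negative symptoms are not tested separately.

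The first assumes standardised scores. The second assumes that all three visits enter, with the same 0.8 SD difference at both follow-ups. The third needs only the literal reading of the PANSS sentence. No single power figure can be attached: under the assumptions shown it runs from 56% to 91%, and the 56–63% part is one scenario only. The sample size of 70 is unaffected.

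**What to change.** Rewrite the two model sentences in Statistical analyses:

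- Make visit (baseline, 1 month, 3 months) the within-subject factor and group the between-subject factor, with the score as dependent variable.
- Fit a separate model for each outcome: an MCCB score on a common standardised scale, PANSS negative, and PANSS positive. Education and duration of illness can stay as covariates.
- Take the efficacy test from the group-by-visit contrast at follow-up, or from the follow-up difference adjusted for the baseline score. Do not take it from the overall group main effect.

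If the authors already intended one analysis per score over visits, the same rewrite makes that explicit. It costs two sentences and no new data or patients. It should be done and dated before the allocation is unblinded; Trial status describes the trial as ongoing.
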